### Interference

Interference occurs when outcomes for any given unit depend, not only on its own treatment status, but also on the profile of treatments for others units in the experimental group. In the extreme case where control units benefit as much as the treated units from a given treatment profile the estimated ATE will be zero even though the treatment might have been hugely beneficial. There is an effect but no primary effect (conditional on interference) [57]. To test for the presence of interference and control for it we need to assume a model of interference. In our discussion with employees of the ASF we learned that municipal officials talk to each other with regards to the audit program. We will assume talking is along party lines and limited to other municipalities in the same state (parties are organized around states). (Geographic distance between municipalities may not be that important considering the degree of cell phone and email penetration in Mexico but we might consider it in a secondary analysis). We will also assume that the intensity of talking depends on the similarity of the municipalities, as they are more likely to have interests in common. We will proxy for similarity using FISM grant amounts. These are decided by a formula (and some gubernatorial discretion) that takes as inputs socio-economic indicators. We check for interference using municipalities outside the experimental group (their exposure is random [52]) using administrative data from the Federal Treasury detailing what categories of municipal public goods municipalities invest in and their rate of disbursements. Specifically we proceed as follows: We define the distance measure for municipality *i* in experimental state *j* as , where *x*_*i**j*_=1 if at least one of the audited municipalities in state *j* has a major with the same party affiliation as municipality *i*, and where  is the amount of FISM transfers (*w*_*i**j*_) received by municipality *i* in state *j* as a fraction of the average transfer received by audited municipalities of the same party affiliation () in the same state *j*. If none of the audited municipalities share a party affiliation we set *y*_*i**j*_=0. To ensure *y*_*i**j*_∈ [ 1,0) we only calculate the measure for municipalities that receive same or lower transfers than those in the experimental group.Since our distance measure is continuous, we stratify municipalities into quartiles defined by *y*. Along with the binary *x*, this defines a 4×2 table of outcomes, where one column is units treated with spillover effects of magnitude *y*_*q*_ and the other column is assumed to receive no spillover.As noted, dependent variables will be derived from the PASH files which cover almost all municipalities in Mexico. These include whether municipalities report to the Federal Treasury, what categories of municipal public goods they invest in, and the rate of disbursements among other.

Given the definition of the distance measure and the fact that experimental municipalities are also blocked on *y* finding strong evidence of spillover effects would severely compromise the detection of ATE within the experimental group using the survey data. That said, we can proceed as above and define *d*_*i**j*_ for each municipality in the experimental group (by definition treated municipalities score a 1). Since these have already been blocked on *y* most of the variation – if any – will come from the party affinity measure within the block. As usual we can proceed by testing a family of sharp nulls where we classify as treated all municipalities with *d*_*i**j*_>0 and control otherwise. Rejecting the sharp null would suggest treatment and its spillover has an effect. If so we can further test the no null of no effect between treated units and those subject to spillover by defining treated as those with *d*_*i**j*_=1 and control as those with 0<*d*_*i**j*_<1. For estimation we use inverse probability weights [52].

In conclusion, the block randomized, controlled, three-arm parallel group exploratory AUDIT study on a convenience sample of 85 municipalities in Mexico fulfills standard scientific criteria for evidence-based evaluation [58], and reporting (see Additional file 1). We are confident the aforementioned measures to deal with threats to inference will be sufficient to ensure the AUDIT study will meet its objectives. Namely, to assess the efficacy of the national program of audits in improving compliance with a federal grant program to improve municipal infrastructure. And to explore the mechanisms by which any effects take place; the influence of institutional differences; and potential synergies with local accountability systems. Finally, the study design also demonstrates the use of verifiable and replicable randomization, and of sequentially partitioned hypotheses to reduce the Type I error rate in multiple hypothesis tests.

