## Methods/Design

### Trial design

The AUDIT study is a block randomized, three-arm parallel group, exploratory trial on a convenience sample of 85 municipalities in Mexico. Blocking was done by state across 17 states, with five municipalities per block. Using non-uniform random assignment and a 1:1:3 blocking ratio we assigned one municipality per block to be audited by the ASF, another by the EFSL, and the remaining three municipalities to the control condition (no intervention). Our reporting of the trial design follows the CONSORT 2010 Checklist [39, 40] (See Additional file 1). The trial received an ethics approval by Yale University’s Human Subjects Committee (ref: 1106008610), and is registered with the International Standard Randomised Controlled Trial Number Register (ISRCTN22381841) and the Experiments in Governance and Politics Network (No:20121031). All end line survey participants are required to give informed consent.

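### The spillover check calls the exposure of outside municipalities random, but exposure is set by state and party and is impossible or certain for some groups, so its table and estimates partly compare parties

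*Protocol article*

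**What the plan says.** The Interference section of the Protocol article assumes that officials talk along party lines within their state. It then states: "We check for interference using municipalities outside the experimental group (their exposure is random [52". The exposure indicator x for municipality i in state j is "1 if at least one of the audited municipalities in state" j "has a major with the same party affiliation as municipality" i. A similarity measure y, based on FISM transfers, is cut into quartiles. Together with x, "this defines a 4×2 table of outcomes, where one column is units treated with spillover effects of magnitude" y, and the other column is assumed to receive no spillover. The only restriction on outside municipalities at this step is on the size of their transfers. None concerns their chance of being exposed.

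The section says what hangs on the result: "finding strong evidence of spillover effects would severely compromise the detection of ATE within the experimental group using the survey data".

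Other parts of the article bear on the point:

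- **Trial design:** "Blocking was done by state across 17 states, with five municipalities per block"; and "we assigned one municipality per block to be audited by the ASF, another by the EFSL, and the remaining three municipalities to the control condition".
- **Randomization and interventions:** the assignment probabilities are known exactly, and 4 ASF and 3 EFSL assignments are non-uniform.
- **Statistical methods:** randomization tests of the sharp null are the general default. Robust OLS remains possible for modelling.
- **End of Interference:** inverse probability weights are used for estimation. That sentence closes a paragraph on the experimental municipalities, so it is unclear whether it reaches the table of outside municipalities.

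**The concern.** The lottery drew study municipalities; it did not draw outside ones. An outside municipality's x follows from its state and party alone, so a whole state-by-party group is exposed together or not at all. The chance of exposure depends on how many of the state's five study municipalities that party governs, which the lottery did not decide. A party governing none of the five can never be exposed, and one governing four or five always is. If such groups stay in the table, one column gathers parties that are weak among a state's study municipalities and the other gathers strong ones.

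If reporting to the Treasury, spending categories or disbursement rates differ by party, the columns will differ without any spillover. The article says that strong evidence of spillover would seriously weaken the main comparison on the survey outcomes, so an artefact here could discredit a sound randomised result.

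**Working it through.** **Inputs from the article.** 17 states; five study municipalities per state; one assigned to ASF and one to EFSL; x as quoted above; the 35-digit vector in Table 2. I read audited municipalities in the definition of x as those assigned by the lottery.

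**1. The article's own figure.** Table 2 gives 23862, 19186, 54595, 42585, 02437, 45776, 09502. The first digit of each number can only be 0 to 5. These digits stand at positions 1, 6, 11 and 16 (within the 17 ASF draws) and at 21, 26 and 31 (within the next 17). That reproduces 4 ASF and 3 EFSL.

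**2. Exposure probability, uniform draws.** Let a party govern k of the five study municipalities. Its group is unexposed only if both audits fall on the other 5 − k:

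P(x = 1) = 1 − C(5 − k, 2)/C(5, 2), with C(5, 2) = 10.

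| k | C(5 − k, 2) | P(x = 1) |
|---|---|---|
| 0 | 10 | 0 |
| 1 | 6 | 0.4 |
| 2 | 3 | 0.7 |
| 3 | 1 | 0.9 |
| 4 | 0 | 1 |
| 5 | 0 | 1 |

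**3. States with a non-uniform draw.** If the ASF digit is restricted, the first three listed municipalities each have ASF probability 1/3 and the last two have 0. EFSL is then 1/4 for each of the four that remain.

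- k = 1: 1/3 + (2/3)(1/4) = 0.50 for one of the first three; 0 + 1/4 = 0.25 for one of the last two.
- k = 2: 0.50 to 0.83.
- k = 3: 0.83 to 1. The value 1 occurs when the party governs exactly the first three.

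For a restricted EFSL digit, k = 1 runs from 0.20 to 0.53 if a clash with the ASF municipality is re-drawn from the same restricted digits. If a clash passes to the next, unrestricted digit, as the note to Table 2 describes, k = 1 is 1/5 + (3/5)(1/3)(1/4) = 0.25 for the last two and 1/5 + (2/5)(1/3 + 1/12) + (2/5)(1/3) = 0.50 for the first three. Under either rule the k = 3 group made up of the first three reaches 1.

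**4. What this does to the table.** A group with P = 0 has no exposed counterpart under any draw, and its weight 1/P does not exist. A group with P = 1 has no unexposed counterpart, and 1/(1 − P) does not exist. Between these, groups at 0.4, 0.7 and 0.9 enter the exposed column at unequal rates. The unweighted contrast therefore needs both restriction and weighting.

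**5. Size, by simulation with no spillover.** The article gives no party shares, number of outside municipalities or clustering, so these are assumptions: three parties with average shares 50/30/20% varying by state; 20 or 50 outside municipalities per state; intraclass correlation (ICC) within state and party of 0 to 0.10; the largest party differing from the others by 0 or 0.3 SD; uniform lottery; no restriction on transfers and no quartiles. Each row uses 400 trials with 99 re-draws. About 35% of outside municipalities had P exactly 0 or 1.

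| Outside per state | ICC | Party difference (SD) | Rejects: independent units | Rejects: lottery re-draw, unweighted | Rejects: lottery re-draw, 0<P<1, weighted | Mean difference, unweighted (SD) | Mean difference, 0<P<1, weighted (SD) |
|---|---|---|---|---|---|---|---|
| 20 | 0 | 0 | 6.8% | 2.5% | 2.8% | 0.000 | −0.001 |
| 20 | 0.05 | 0 | 9.8% | 4.8% | 5.0% | 0.009 | 0.009 |
| 20 | 0.10 | 0 | 12.2% | 3.5% | 3.2% | 0.007 | 0.010 |
| 20 | 0 | 0.3 | 11.5% | 3.2% | 4.0% | 0.071 | 0.004 |
| 20 | 0.05 | 0.3 | 19.0% | 3.8% | 3.0% | 0.087 | 0.024 |
| 50 | 0 | 0 | 3.8% | 4.0% | 3.0% | −0.004 | 0.001 |
| 50 | 0.05 | 0 | 18.2% | 5.8% | 5.5% | 0.000 | 0.005 |
| 50 | 0.10 | 0 | 27.5% | 5.0% | 5.2% | −0.005 | −0.005 |
| 50 | 0 | 0.3 | 24.8% | 3.8% | 5.8% | 0.078 | 0.007 |
| 50 | 0.05 | 0.3 | 33.5% | 3.8% | 2.2% | 0.079 | 0.006 |

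Monte Carlo error of the rejection rates is about 1 to 2.4 points. The re-draw tests hold the nominal 5% even with the groups at 0 and 1 left in. The unweighted difference is displaced by 0.07 to 0.09 SD whenever parties differ by 0.3 SD.

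**The case against.** The strongest reply is that the article prescribes no municipality-level test. The Interference section defines a table and names no standard error. The stated default is a randomization test, and re-running the lottery moves whole state-by-party groups together and leaves the groups at 0 and 1 where they are. Such a test is valid, as the simulation shows. The article also mentions inverse probability weights and refers to a detailed analytical plan that is not shown. And the check is a diagnostic in an exploratory trial: after the warning about spillover the section goes on to further sharp-null tests and attaches no stopping rule.

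Much of this stands. A reader might infer that the check will report spillover falsely at rates such as 10% to 34%. The article does not support that. Those rates belong to a test of municipalities as independent units, which the text leaves open but does not prescribe. They also rest on an assumed ICC and assumed party differences; with neither, the rates are 6.8% and 3.8%. A reader might also infer that the check decides whether the main analysis goes ahead. The text does not say so.

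The reply leaves two things untouched. The statement that outside municipalities' exposure is random is made in the article itself and is wrong for identifiable groups, so it is not a detail left to another document. And a valid p-value does not correct the tabulated difference or an estimate taken from it.

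**Conclusion.** The concern holds as a defect in the premise of the check and in its table and estimates. It does not hold as a demonstrated inflation of false positives. That exposure is shared within state-by-party groups, and that its probability is 0 or 1 for some values of k, follows from the article's own definitions. Which groups are affected depends on the actual party affiliations, which the article does not give.

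The displacement of 0.07 to 0.09 SD is conditional on parties differing by 0.3 SD and on the assumed shares. With no party difference, the mean unweighted difference stayed within 0.01 SD of zero. After restriction to 0 < P < 1 and weighting, it was 0.004 to 0.024 SD in the settings with a party difference. The correction is worth making because the article itself ties a finding of spillover to the credibility of the main result.

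**What to change.** In the Interference section:

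1. Compute each state-by-party group's exposure probability from the actual lottery rules, including the seven non-uniform draws and the rule for a digit that falls on the ASF municipality.
2. Limit the table and all estimates for outside municipalities to groups with 0 < P < 1, and weight by these probabilities. Report how many municipalities are left out at 0 and at 1.
3. State that the randomization test of the Statistical methods section applies to this check, with the lottery re-run and x derived afresh for whole state-by-party groups each time.
4. Confine the statement that exposure is random to this subset.

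The cost is a few sentences and a short program; party affiliation and the lottery probabilities are already needed. The downside is that fewer outside municipalities enter the check and its precision falls.

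### The spillover check's quartile table has no unexposed comparator in at least three of its four rows, and its second study-group test has no class for unaudited municipalities scoring above 1

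*Protocol article*

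**What the plan says.** All the rules below are in the Interference part of the article's Discussion.

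- **Exposure, x.** A municipality has x=1 if at least one audited municipality in its state has a mayor of the same party.
- **Similarity, y.** This is the municipality's own FISM transfer "as a fraction of the average transfer received by audited municipalities of the same party affiliation" in the same state. For municipalities with no match: "If none of the audited municipalities share a party affiliation we set" y to 0.
- **Bound on y.** To keep y from exceeding 1, "we only calculate the measure for municipalities that receive same or lower transfers than those in the experimental group".
- **Outside municipalities.** "Since our distance measure is continuous, we stratify municipalities into quartiles defined by" y. With the binary x, "this defines a 4×2 table of outcomes, where one column is units treated with spillover effects of magnitude" given by the quartile, and "the other column is assumed to receive no spillover".
- **Study municipalities.** The same procedure gives each a score d, and "by definition treated municipalities score a 1". The first test compares d>0 with d=0. If it rejects, "we can further test the no null of no effect between treated units and those subject to spillover", with treated meaning d=1 and control meaning 0<d<1. Estimation uses inverse probability weights.

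**The concern.** Two of these rules conflict with the definitions they rest on.

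First, stratifying on y should let exposed and unexposed municipalities of similar transfer size be compared. But y carries information on size only for exposed units. For unexposed units it is a constant, so the strata cannot match the two columns.

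Second, the bound on y is secured by a restriction written for municipalities outside the experiment. Inside it, an unaudited municipality can receive more than the audited ones, and the cut-offs of the second test make no provision for that.

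The article says that strong evidence of spillover would seriously weaken detection of the average treatment effect from the survey data. It also assumes non-interference for effect estimates and confidence intervals (Statistical methods). A check with that role should give a stratified comparison and a classification that can be carried out as written.

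**Working it through.** The article gives no figure of its own for this analysis, so there is none to reproduce. The inputs are the worded definitions above, the selection of ranks 6 to 10 by transfer within each state (Participants), and the transfers and allocations in Table 2, in millions rounded to whole numbers. Two things are assumed. The equation for d is not legible in the text available for review, so d = x × y is used because it fits the stated classes d=0, 0<d<1 and d=1. Party affiliations are not given, so several patterns are shown.

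**Step 1: the 4×2 table.** This step needs only the wording, not the equation for d. If x=0 then y=0, so all unexposed units are tied at the lowest value and fall in one row. The other three rows hold none. Take 1,000 municipalities with quartiles cut over all of them:

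| Unexposed | Lowest row: exposed / unexposed | Rows holding both kinds |
|---|---|---|
| 10% | 150 / 100 | 1 of 4 |
| 20% | 50 / 200 | 1 of 4 |
| 25% | 0 / 250 | 0 of 4 |
| 30% | 0 / 300 | 0 of 4 |
| 50% | 0 / 500 | 0 of 4 |

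If the quartiles were cut among exposed units only, the unexposed would lie below all of them and still could not be spread over the rows.

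**Step 2: scores of unaudited study municipalities.** Score = own transfer / mean transfer of same-party audited municipalities. In Chiapas the audited units are at 61 (ASF) and 68 (EFSL), and the controls at 69, 65 and 59.

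| Party shared with | Audited mean | 69 | 65 | 59 |
|---|---|---|---|---|
| both | 64.5 | 1.070 | 1.008 | 0.915 |
| ASF unit only | 61 | 1.131 | 1.066 | 0.967 |
| EFSL unit only | 68 | 1.015 | 0.956 | 0.868 |

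Rounding, when party is shared with both:

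- The control at 69 lies between 68.5/65.0 = 1.054 and 69.5/64.0 = 1.086, so it is above 1.
- The control at 65 lies between 64.5/65.0 = 0.992 and 65.5/64.0 = 1.023, so it is borderline.

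With the EFSL unit only, the control at 69 ranges from 68.5/68.5 = 1.000 to 69.5/67.5 = 1.030.

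In Chihuahua (audited 15 and 13; controls 12, 11 and 13) no control exceeds 1. If party is shared only with the EFSL unit, the control at 13 scores 13/13 = 1.000 on the rounded figures.

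There are 2^5 = 32 ways to label five municipalities with two parties, giving 32 × 3 = 96 control scores per state under the actual allocation. In Chiapas 40 of 96 exceed 1, and in Chihuahua 8 of 96 equal 1. These counts show what can happen. They are not probabilities.

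By the ratio, the audited Chiapas units would score 61/64.5 = 0.946 and 68/64.5 = 1.054 if they share a party. Their score of 1 is therefore a convention, not a result of the formula.

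**Step 3: exposure probabilities.** Let k of the five study municipalities share a given municipality's party. If the two audited were drawn uniformly and only study audits counted, P(x=1) = 1 − C(5−k,2)/C(5,2) = 0, 0.4, 0.7, 0.9, 1, 1 for k = 0 to 5. The middle values depend on uniformity, which the article says fails in some blocks (Randomization and interventions). The value 1 at k = 4 or 5 does not, because two audits cannot both miss the party.

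**The case against.** The strongest reply is that the table can be read as a dose gradient: each exposure quartile is set against one common group assumed to receive no spillover. On that reading comparators exist. This stands as far as it goes, and so does a pooled x=1 versus x=0 contrast. Neither compares units of similar transfer size, however, which is what stratifying on y would be for.

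On the study group, it is fair to say that the intended groups of the second test are plain from the wording, that assignment is known, and that the detailed analytical plan is in Additional file 2, which is not shown. A sensible analyst would probably use assignment. But the article states the cut-offs outright, and they leave unaudited units above 1 without a place. Extending the transfer restriction to study municipalities would not help, since those units would then be removed by the restriction.

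It is also true that the scores above 1 rest on an assumed equation and an assumed party match. The table problem rests on neither.

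The exposure series in step 3 is open to two further objections. It assumes uniform selection, and it counts only the two study audits per state, whereas 43 other municipalities were pre-selected for the 2011 program and the article does not say whether they count as audited. Both stand, so the series is illustrative only.

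**Conclusion.** Two stated rules fail as written.

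1. **The quartile table** lacks an unexposed unit in at least three of four rows. With quartiles over all units, it has no row with both kinds once 25% or more are unexposed.
2. **The second study-group test** has no class for an unaudited municipality whose transfer exceeds the mean of its same-party audited municipalities. This assumes d = x × y and a shared party. The Chiapas control at 69 million is the clear example. Who is excluded depends on the lottery, and every control that stays in has a transfer below that mean by construction.

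A reader might infer more than the article supports:

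- That the whole interference analysis is unusable. The d>0 versus d=0 test is not affected by scores of 1 or more, and the pooled contrast survives.
- That controls would commonly be counted as treated. That needs an exact tie, and the only example comes from rounded figures. Exclusion is the usual consequence.
- That two of three Chiapas controls certainly drop out. Even when party is shared with both audited units, the one at 65 million is borderline.
- That this check settles the main result. It is supplementary in an exploratory trial whose inference starts from randomization tests of the sharp null.

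The point should be corrected. It does not undermine the trial's primary tests.

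**What to change.** - **Study municipalities.** Take treated status from the assignment variable. Classify the rest as unaudited with, or unaudited without, a party match. Drop the d=1 and d<1 cut-offs.
- **Similarity.** Define it for every municipality independently of x, so that quartiles exist in both columns. One option is the transfer relative to all audited municipalities in the state, which stays close to the assumed mechanism but changes with the draw. The other is the transfer relative to the mean of the five study municipalities, which is fixed before the draw but no longer measures closeness to the audited ones. State which is used.
- **Exposure probabilities.** Compute them from the actual non-uniform lottery, say which audits count as exposure, and limit inverse-probability-weighted estimates to units with a probability strictly between 0 and 1.

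The cost is revised wording and a little coding. Some outside municipalities, whose exposure is certain or impossible, leave the weighted estimate.

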### Randomization and interventions

We use a verifiable and replicable block randomization procedure based on publicly available state lottery numbers. The chosen method had to meet two major constraints. First, it had to be sufficiently simple that the ASF could explain, justify, and replicate the randomization mechanism to Congress. Second, the randomization process had to be compatible with the operational and technological infrastructure of the implementing agency (effectively limiting software solutions to Microsoft Excel). The experimental group consists of 17 blocks with 5 municipalities each. Using non-uniform random assignment and a 1:1:3 blocking ratio we assigned one municipality per block to be audited by the ASF, another by the EFSL of the block’s state, and the remaining three municipalities to the control condition (no intervention). Specifically the block randomization process proceeded as follows: By state, we provided each municipality with a pair of single-digit “tickets”:Block municipalities by stateIn Excel list municipalities in increasing order based on their individual identifier provided by the Mexican National Institute of Statistics and Geography (INEGI, in Spanish).Assign each municipality two single-digit “tickets”, and do this sequentially for all municipalities (e.g. 0-1, 2-3, 4-5, 6-7, 8-9 …).We generated a random vector of “winning digits”:To generate the random “winning digits”, we used the winning numbers of the seven largest prizes of the Mexican National Lottery of the first Tuesday of March 2011.Each winning number has 5-digits.We ordered the 5-digit winning numbers in decreasing order of prize.Our first five “winning digits” come from the number associated with the highest prize (e.g. for the date we used, the number was 23862 and the price 5 million pesos), the next ten “winning digits” digits come from the second and third prizes.The fourth largest prize (of 80,000 pesos) was won by four numbers. To order these tied lottery numbers randomly, we (1) ordered the numbers in increasing order; (2) grab the number associated with the largest prize in the lottery of 22 February (e.g. number 36625), delete one repeated digit (e.g. becomes 3625); (3) assign one of these digits to each of the four tied lottery numbers; (4) use this assigned digit to sort the four tied lottery numbers in increasing order (e.g. 2,3,5,6).Concatenating the 15 “winning digits” from three lottery numbers associated with the three top prizes, and the random ordering of the four lottery numbers tied for fourth prize, gives us a random vector of 35 “winning digits”, enough to randomly assign 17 municipalities to ASF audit, and 17 municipalities to EFSL audit.We then assigned municipalities to treatment arms based on the random vector of “winning digits”:Start reading from the top of the vector of “winning digits”. The first winning digit is a 2, so assign the municipality in the first state holding the single-digit “ticket” 2 to an ASF audit. Then, use the second “winning digit” from the vector to assign a municipality in the second state to ASF audit, and so on for all 17 states.Repeat the procedure – starting from the 18^th^ element of the vector of winning digits – to allocate one municipality by each of the seventeen states to an audit by the EFSL.Municipalities not allocated to EFSL or ASF serve as control.

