Because the treatment was randomized with known probabilities we rely on randomization tests of the sharp null of no effect on any unit [49]. The specific randomization statistic chosen will be appropriate to the category and distribution of the outcome measures. We will use sequential partitioned hypothesis testing to address the multiplicity of analyses and outcomes and control the Type I error rate [50, 51]. We will let exploratory data analysis and model checking determine whether we model the outcome by inverting randomization tests or via robust OLS estimation, though our default is to rely on additive effects and inversion of sharp null hypothesis tests (see Annex A). Finally, whereas the treatment was randomized to municipalities, some outcome variables are measured at the level of individual municipal administrators. At this level the treatment can be thought of as cluster randomized. We will analyze these data at the individual level and check for robustness by comparing inferences to a differences in total outcomes estimator and to aggregating individual level at the municipal level [52]. A detailed analytical plan is available as Additional file 2.

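### The second spillover test (audited versus spillover-exposed) is not sharp for the full lottery, and its type I error is not controlled if it is run with ordinary full-lottery redraws

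*Protocol article*

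**What the plan says.** Under Statistical methods, the protocol article sets the general approach: "Because the treatment was randomized with known probabilities we rely on randomization tests of the sharp null of no effect on any unit".

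The Interference section defines an exposure score d for each municipality in the experimental group. Audited units sit at the top ("by definition treated municipalities score a 1"). Controls that share a party with an audited municipality in the same state have intermediate values, scaled by grant size. Zero applies otherwise: "If none of the audited municipalities share a party affiliation we set" the score to 0.

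Two tests follow. The first compares d>0 with d=0: "As usual we can proceed by testing a family of sharp nulls where we classify as treated all municipalities with" d>0. On its result the article says: "Rejecting the sharp null would suggest treatment and its spillover has an effect". Only then comes the second test, d=1 against 0<d<1: "If so we can further test the no null of no effect between treated units and those subject to spillover". The article gives no separate reference distribution for it. For estimation in this analysis it names inverse probability weights.

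**The concern.** There are three exposure levels: audited, exposed through a party link, and unexposed. The second null equates the first two and leaves the third free.

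A randomization test holds outcomes fixed across redraws, which is legitimate only when the null says what each unit's outcome would have been under every redraw. Here a redraw can make an unexposed control exposed or audited, or make an exposed control unexposed. The second null does not supply those outcomes. Holding them fixed amounts to assuming that no level of exposure matters, and the second test is reached only after that assumption has been rejected.

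At stake is the conclusion drawn once interference has been found, namely whether an audit does anything beyond what spillover does. A miscalibrated test could report a direct effect that is not there, or miss one that is.

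**Working it through.** **Inputs from the article.** "The experimental group consists of 17 blocks with 5 municipalities each", so 17 × 5 = 85. One federal and one state audit per block gives 2 × 17 = 34 audited and 85 − 34 = 51 controls, as the article states. It gives no error rate for the spillover tests, so there is no figure of its own to reproduce.

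**Assumptions, not in the article.** Party shares as listed below; outcome SD of 1; party unrelated to baseline outcome; any same-party control counts as exposed; spillover equal to the direct effect (delta), so the second null is true; alpha 0.05.

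**Hand example, one hypothetical block.** Three municipalities belong to party A and two to party B. Outcomes are 0 if unexposed and 1 if audited or exposed. The actual draw audits two As.
- Outcomes: A = 1, 1, 1; B = 0, 0. Audited minus exposed = 1 − 1 = 0, as the null says.
- The full lottery has 10 pairs: 3 AA, 6 AB, 1 BB.
- AA redraws: difference 0.
- AB redraws with outcomes fixed: audited mean (1 + 0)/2 = 0.50; exposed mean (1 + 1 + 0)/3 = 0.67; difference −0.17.
- BB redraw: no exposed control, so no contrast.
- Centre over the 9 usable redraws: (3 × 0 + 6 × (−1/6))/9 = −0.11, not 0.
- Redraws that keep the same units at d>0 are the 3 AA pairs, and all give 0.

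Had the actual draw audited both Bs (B = 1, 1; A = 0, 0, 0), the AB redraws would give 1/2 − 1/3 = +0.17. The displacement can therefore go either way within a block.

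**Simulation of the whole design** (1000 trials, 500 redraws each; Monte Carlo SE at 5% is √(0.05 × 0.95/1000) = 0.007). Rejection rates under a true second null:

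| Party shares | delta (SD) | First test rejects | Full lottery, doubled tails | Full lottery, absolute difference | Full lottery, IPW statistic | Redraws keeping the d>0 set |
|---|---|---|---|---|---|---|
| 60/40 | 0 | 0.042 | 0.049 | 0.046 | 0.044 | 0.046 |
| 60/40 | 1 | 0.614 | 0.051 | 0.039 | 0.046 | 0.051 |
| 60/40 | 2 | 0.967 | 0.055 | 0.024 | 0.040 | 0.049 |
| 50/30/20 | 0 | 0.044 | 0.062 | 0.058 | 0.063 | 0.057 |
| 50/30/20 | 1 | 0.870 | 0.064 | 0.030 | 0.035 | 0.048 |
| 50/30/20 | 2 | 1.000 | 0.120 | 0.018 | 0.032 | 0.048 |
| 30/30/20/20 | 0 | 0.044 | 0.044 | 0.055 | 0.046 | 0.034 |
| 30/30/20/20 | 1 | 0.956 | 0.086 | 0.035 | 0.038 | 0.062 |
| 30/30/20/20 | 2 | 1.000 | 0.156 | 0.004 | 0.025 | 0.041 |

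On average about 12 to 28 of the 85 municipalities sit at d=0. At delta = 0 every version is close to nominal, as it should be. Otherwise the full-lottery reference is centred at about −0.06 to −0.15 SD for delta = 1 and −0.12 to −0.28 SD for delta = 2.

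Across repeated runs at 1 to 2 SD, including a 40/30/20/10 party mix, the raw difference rejects about 8–26% one-sided and about 4–17% with doubled tails. The restricted redraws stay at 3.4–6.2% in all 12 scenarios of the tabulated run, which also included delta = 0.5.

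**The case against.** The strongest reply is that the article does not commit the error. It uses the word sharp for the first test, not the second, and it fixes no reference set for the second. A test conditional on the exposed set fits its wording. It also defers to a detailed analytical plan (Additional file 2), which is not shown. This stands as a limit: a reader might infer that the second p-value is simply wrong, but that follows only if the full lottery is used. It does not remove the point, because the full lottery with outcomes fixed is the only reference distribution the article describes, and the second test is introduced as a continuation of the first.

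A reader might also infer that the test leans towards declaring that audits work beyond spillover. It does so for one-sided tests of the raw difference, and for doubled-tail tests mainly with three or more parties. Absolute-difference and inverse-probability-weighted statistics are conservative, and doubled tails with two parties are near nominal. The article leaves the statistic open.

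A third inference, that the estimated direct-minus-spillover effect is biased because test inversion is the general default, is not supported: the Interference section names inverse probability weights for estimation here.

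Finally, the simulation treats exposure as same-party or not, while the article scales it by grant size. In the Chiapas example of Table 2 the audited units receive 61 and 68 million (mean 64.5). A same-party control at 69 would have ratio 69/64.5 = 1.07, which does not clearly fall in 0<d<1. That also stands. Restricting redraws is valid if the second null is read as equal outcomes at every d>0, and the plan should say so.

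**Conclusion.** The point holds in conditional form. The second spillover null is not sharp for the full lottery. Run with full-lottery redraws and fixed outcomes, the test relies on the null rejected one step before, and its type I error is not controlled. That much is logic and needs no simulation.

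The size does depend on assumptions: the party mixes, a constant spillover equal to the direct effect at 1 to 2 SD, and binary exposure. Under these, actual error at nominal 5% runs from about 1% or below to about 26%, according to statistic and sidedness. No fixed direction can be claimed.

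This is a contingent check in an exploratory trial, and none of H1–H14 concerns spillover, so the main hypotheses are not directly affected. It is still worth settling in advance: the article expects officials to talk along party lines, and the analysts are not blind to allocation.

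**What to change.** State that the second test, and any inversion of it, uses only lottery draws that leave the same municipalities at d>0 in each block. Weight those draws by their known probabilities, since 4 federal and 3 state assignments were non-uniform. Re-label audited versus exposed only within those draws. State that the null is equal outcomes at every d>0, how a control with a grant ratio of 1 or more is classified, and which statistic and sidedness apply.

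The cost is a sentence or two and a change of code, with no new data. Blocks with a single admissible draw contribute nothing. In the simulated designs about 83–94% of blocks still contributed, so some power is lost.
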